## Follow-up of adverse events

All AEs will be followed until they have abated, or until a stable situation has been reached. Depending on the event, follow up may require additional tests or medical procedures as indicated, and/or referral to the general physician or a medical specialist.

# 8. STATISTICAL ANALYSIS

The collected data will be analyzed through SPSS 19 and two different outcome values will be calculated. The different outcome values are:

- Mean and standard deviation of segment intervals (PQ, QRS, ST etc.) with 95%

confidence intervals

- Mean and standard deviation of amplitudes of the P – top, QRS complex and the

T – top with 95% confidence intervals.

- The heart axis of the fetus

After analysis of these sub-groups (fetuses with the same form of severe CHD in one group, all the healthy fetuses in one group) in SPSS, the different intervals of the fECG of the cross-sectional study and the case-cohort study will be compared with one another through a t-test or a Mann-Whitney-Wilcoxon-test to investigate whether or not there is a repetitive pattern to be recognized. This depends from the normal distribution and the quantity of the collected data. The research is quantitative.

The questionnaires will be analyzed. We will evaluate per fetus if the conducted data from the cross-sectional population is usable and if the data of this particular patient should be excluded due to a missed diagnosis of congenital heart disease during the pregnancy.

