# 1. INTRODUCTION AND RATIONALE

During pregnancy, multiple ultrasound examinations are performed to assess the fetal condition. This is executed, amongst others, during or around week 20 of gestational age and is called the fetal anomaly ultrasound (SEO in Dutch). With this technique, all kind of possible congenital anomalies can be detected, including CHD. However, a false negative diagnosis occurs frequently and the SEO only detects 25 to 60 per cent of the patients with CHD^1, 2^. That makes CHD the most common structural fetal abnormality of which a significant part is missed during the prenatal life.

CHD can be divided into cyanotic and non-cyanotic. An example of cyanotic CHD is Fallot’s tetralogy or a transposition of the great vessels. An example of the non-cyanotic form is an aortic stenosis, atrial septum defect or an aortic coarctation. The incidence of CHD is estimated to be 4 to 9 per 1000 live born^3^. In the Netherlands, the overall incidence of anomalies of the vascular system is estimated at 6,6 per 1000 live births^4^. The incidence of severe CHD (read, of hemodynamic importance) is low (see appendix I. page 27).

The survival for patients with CHD is low, 21 percent^2, 3^, and the prognosis is negatively influenced by the presence of heart failure, aneuploidy or extracardial malformations. There are several studies which show a correlation between an abnormal heartbeat of the fetus and the diagnosis CHD. These patterns can be diagnosed with ultrasound (including the Doppler technique), which is the current method for prenatal screening of CHD. If a CHD is suspected or seen on the SEO, the patient will receive a more intensive ultrasound, named the GUO (geavanceerd ultrageluids onderzoek) in Dutch. If the CHD is confirmed with the GUO, the fetus has a high certainty of having a CHD. In 2003, the Dutch magazine of medicine (in Dutch: Nederlands tijdschrift voor geneeskunde) reported a sensitivity of 94,7%, a specificity of 98,8%, a positive prognostic value of 95,3% and a negative prognostic value of 98,6%^5^

However, these routine controls with ultrasound can only diagnose about 25 to 60 per cent of the large heart defects^1, 2^. The disadvantage of Doppler ultrasound is that there can be false – negatives. Plus the fact that Doppler can’t detect beat – to – beat heart rate, which causes several heart abnormalities to be missed.

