We expect that the fECG can detect severe heart conditions early in pregnancy, with the possibility of adequate early treatment in the future. Nowadays, there are options of operating during pregnancy to optimize the outcome of the fetus with CHD.

We hypothesize that the non-invasive fECG combined with the SEO has a higher detection rate for diagnosing CHD compared to the SEO alone. We expect that the fECG can detect additional details about the development and etiology of CHD. More knowledge about fetal heart rhythms and abnormalities of the different intervals and heart axis in a fECG are needed to optimize the diagnosis and management of CHD.

The summary of the most occurring ECG findings of the most common CHD can be found in Appendix II, page 28.

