# 6. METHODS

## Study parameters/endpoints

### Main study parameter/endpoint

In the cross-sectional study, the main study parameter is the determination of the normal value or range of amplitude and segment intervals with 95% confidence intervals of the fECG of a healthy fetus.

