### Secondary study parameters/endpoints (if applicable)

The case-cohort study focuses on the abnormal value or range of amplitude and segment intervals in fetuses with diagnosed severe CHD, and compares these with the values found in the cross-sectional study.

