## Study procedures

All the patients will undergo a non – invasive, transabdominal fECG during regular outpatient clinic appointments, performed by one of the researchers. This test has a very low grade of discomfort for the patient. The conducted fECG will be stored on an external hard drive, the data will be analyzed by researchers of the Technical University. The last two investigators will look at the fECG and will determine the segment intervals, the heart axis and the amplitudes. After the analysis, we will be able to enter the data in SPSS to conduct normal values and ranges with 95% confidence intervals. The patients will not be notified of any abnormal findings on the fECG, because this is a pilot study. We do not know for certain that any abnormalities we find are actually real abnormalities. This is something we want to investigate.

In the cross-sectional study, we want to know if the fetuses we included are born healthy. Therefore, we will evaluate this with a simple questionnaire which we will send four to six weeks postpartum. We believe this questionnaire will be sufficient to evaluate if any severe CHD was present at birth, because a severe CHD has hemodynamic consequences which present early in neonatal life. Besides, we have permission to withdraw patient information at the postnatal clinic or attending pediatrician. If the neonate has a congenital heart disease missed by the SEO, we will exclude the patient from the cross-sectional study and will evaluate the data of the fECG in the case-cohort study. If the participants do not return the questionnaire, they will be excluded from further analyses.

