## Primary study parameter(s)

The mean and standard deviation of the segment intervals and the amplitudes (with 95% confidence intervals) and the heart axis of healthy fetuses without known CHD.

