# Table 1. Reefhuis J, Samrén EB, Diem MT van. Tables 1981 – 1998. EUROCAT registration of congenital anomalies Northern Netherlands and Southwestern Netherlands. Groningen: University of Groningen, 2000.

# 14. APPENDIX II

| **Congenital defects** | **ECG Findings** |
| --- | --- |
| **Aortic stenosis** | Left ventricle hypertrophy |
| **Atrial septal defect**  **Primum type**  **Secundum type** | Left anterior hemiblock  First-degree AV block  Right axis deviation |
| **Coarctation of the aorta** | Right bundle branch block  Right ventricle hypertrophy |
| **Mitral stenosis** | Right axis deviation  Right ventricle hypertrophy  Right atrial hypertrophy  Left atrial hypertrophy |
| **Pulmonary atresia** | Left ventricle hypertrophy |
| **Pulmonary stenosis** | Right ventricle hypertrophy |
| **Fallot’s Tetralogy** | Right axis deviation |
| **Transposition of the great arteries (complete transposition)**  **Intact ventricular septum**  **VSD and/or PS** | Right atrial hypertrophy  Right ventricle hypertrophy  Right atrial hypertrophy  Biventricular hypertrophy,  right atrial hypertrophy,  bi-atrial hypertrophy |
| **Transposition of the great arteries**  **(“corrected transposition”)** | AV block, 1^st^ to 3^rd^ degree  Atrial arrhythmias (SVT, atrial fibrillation)  Left atrial hypertrophy or bi-atrial hypertrophy |
| **Tricuspid atresia** | Left anterior hemiblock  Left ventricle hypertrophy  Right atrial hypertrophy |
| **Ventricular septal defect**  **Small shunt**  **Moderate shunt**  **Large shunt**  **Pulmonary vascular obstructive**  **disease (Eisenmenger’s syndrome)** | Normal  Left ventricle hypertrophy, left atrial hypertrophy  Biventricular hypertrophy, left atrial hypertrophy  Right ventricle hypertrophy |

Table 2. [name]; [name]. How to read pediatric ECGs. Page 250-251

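### Heart rate and rhythm are part of the case for the fECG but absent from the parameter lists, so a difference in a rate-dependent interval between healthy and CHD fetuses could not be separated from a heart-rate difference

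*Protocol*

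**What the plan says.** Section 1 gives heartbeat and rhythm as part of the reason for the study. It states: "There are several studies which show a correlation between an abnormal heartbeat of the fetus and the diagnosis CHD". It faults Doppler for not giving the beat-to-beat rate and says that abnormalities are missed as a result. It closes with: "More knowledge about fetal heart rhythms and abnormalities of the different intervals and heart axis in a fECG are needed". Section 5.1 describes the abdominal electrodes as a means of determining the fetal rhythm.

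The parameter lists are narrower:

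- Section 6.1.1: "the main study parameter is the determination of the normal value or range of amplitude and segment intervals with 95% confidence intervals".
- Section 6.1.2: "abnormal value or range of amplitude and segment intervals in fetuses with diagnosed severe CHD", set against the healthy values.
- Section 6.3, on what the readers take from each recording: they "will determine the segment intervals, the heart axis and the amplitudes".
- Section 8, first outcome: "Mean and standard deviation of segment intervals (PQ, QRS, ST etc.) with 95" per cent confidence intervals, followed by the amplitudes and the axis.
- Section 8.1: "The mean and standard deviation of the segment intervals and the amplitudes (with 95% confidence intervals) and the heart axis of healthy fetuses".

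Section 8.2 adds the typical fECG patterns in CHD, without defining them. Section 8 compares the intervals of the two study parts by a t-test or a Mann-Whitney-Wilcoxon test, with no covariate and no rate correction. Sections 3 and 4.1 plan 200 healthy fetuses and 10 per CHD type.

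**The concern.** Two things do not fit together. The protocol presents heart rate and rhythm as something the fECG offers and Doppler does not, and then leaves both out of what is read and analysed. In addition, some of the intervals it does analyse can be expected to vary with heart rate: the repolarisation intervals most, PQ less, QRS little. That dependence is general physiology and is not stated in the protocol.

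If healthy and CHD fetuses differ in mean rate, an unadjusted comparison of such an interval mixes two explanations. A CHD group could show a different ST interval only because its hearts beat faster or slower, or a real repolarisation difference could be offset by a rate difference in the other direction. A reader of the results could not tell which, because the rate would not be among the reported variables. At stake is how the secondary comparison is interpreted, not the safety of participants or the conduct of the recordings.

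**Working it through.** **Step 1: is the omission real?** The five lists quoted above (sections 6.1.1, 6.1.2, 6.3, 8 and 8.1) contain amplitudes, segment intervals and, in the last three, the axis. None names heart rate, RR or rhythm. The interval list in section 8 is left open at its end and could include RR, and the patterns in section 8.2 could include rhythm, but neither says so. Section 6.3 matters most in practice, because it fixes which values are extracted and entered in SPSS.

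**Step 2: is there a figure to reproduce?** No. The 200 rests on a cited textbook. Section 4.4 says that no calculation was made for the 10 per CHD type. No alpha, power, SD, heart rate or correlation is given.

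**Step 3: how large could the mixing be?** This is an illustration. From the protocol: n₁ = 10 and n₂ = 200. Assumed: two-sided alpha 0.05; equal SDs; correlation ρ between interval and rate of 0.1 to 0.7; a group difference in mean rate of D = 0.5 to 1.5 SD; and no true conduction or repolarisation difference.

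- Spurious shift in the raw interval, in SD units: s = ρ × D.
- Standard error of the difference, in SD units: √(1/10 + 1/200) = √0.105 = 0.324.
- The test statistic follows a noncentral t distribution with 10 + 200 − 2 = 208 degrees of freedom and noncentrality s/0.324. For ρ = 0.5 and D = 1 this is 0.5/0.324 = 1.54.

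Results for D = 1, as the share of studies with p < 0.05 although only the rate differs. The simulated columns use 4,000 runs per row.

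| ρ | shift (SD) | unadjusted, calculated | unadjusted, simulated | heart rate as covariate, simulated |
|---|---|---|---|---|
| 0.1 | 0.10 | 6.1% | 5.8% | 4.6% |
| 0.3 | 0.30 | 15.2% | 15.4% | 5.6% |
| 0.5 | 0.50 | 33.6% | 34.6% | 4.9% |
| 0.7 | 0.70 | 57.5% | 57.9% | 4.9% |

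The simulation error at 5% is √(0.05 × 0.95/4000) = 0.34 percentage points, so the last column agrees with the nominal 5%.

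Over the whole assumed grid the shift runs from 0.1 × 0.5 = 0.05 SD to 0.7 × 1.5 = 1.05 SD, and the unadjusted rejection rate from about 5% to about 90%.

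**Step 4: what can this comparison detect?** With 10 versus 200, the t-test has about 80% power for a true difference of 0.91 SD, 87% for 1.0 SD and 34% for 0.5 SD. The upper part of the assumed range of spurious shifts is therefore as large as the differences the study could find.

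**The case against.** The strongest reply has four parts.

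1. *The adjustment belongs in a SAP.* How to correct for rate is commonly settled there, and no SAP is shown. This stands for the form of the adjustment. It does not cover the choice of parameters and extracted variables, which sections 6 and 8 of the protocol fix themselves.

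2. *The chosen parameters match the rationale.* Section 1 calls the axis the most important feature and then names amplitudes and intervals. It also says that the heartbeat patterns linked to CHD can be seen on ultrasound. This is fair and weakens any charge of outright contradiction. The remarks on beat-to-beat rate and on the need for knowledge of rhythm remain unanswered by the endpoints.

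3. *A raw difference can still serve detection.* Section 8 looks for a recurring pattern and section 2 for diagnostic value. An interval that differs because of rate still discriminates, and conditioning on rate could remove real disease signal. This stands, and it is why the raw results should stay.

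4. *The size is unknown.* A range from 5% to 90% shows that the answer depends on inputs the protocol does not give. This also stands.

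Three stronger readings are tempting and not supported. A reader might infer that the interval comparison is confounded as a matter of fact, but nothing in the protocol says that mean rate differs in CHD; it speaks only of an abnormal heartbeat. A reader might infer from Appendix II that arrhythmia is to be expected across the enrolled groups. However, "Atrial arrhythmias (SVT, atrial fibrillation" stands only under corrected transposition, and the inclusion criteria name transposition without specifying that form. The other AV-block entry, first-degree block, is under atrial septal defect, which is not on the enrolment list, and it would show in PQ anyway. Finally, a reader might conclude that intervals should come from sinus beats only. With groups of 10, that could discard the data of fetuses with sustained arrhythmia.

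**Conclusion.** The point holds as a gap between rationale and parameters, with a conditional consequence. Heart rate and rhythm are missing from every explicit list, and the stated comparison is unadjusted. If mean rate differs between groups, a difference in ST, QT or, to a lesser degree, PQ cannot be attributed to conduction or repolarisation rather than to rate. For QRS the effect may be negligible.

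The 6% to 58% range rests entirely on the assumed correlations and the assumed 1 SD rate difference. It shows that the effect could matter at 10 versus 200, not that it does. The raw comparison remains a legitimate answer to the detection question. What it lacks is the companion result that would let a reader interpret it. This is a worthwhile and inexpensive improvement, not a flaw that invalidates the study.

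**What to change.** - In sections 6.1.1, 6.1.2, 6.3 and 8, add mean fetal heart rate, derived from RR in the stored recording, as a study parameter for both groups. Note the observed rhythm descriptively.
- Keep the raw interval means, ranges and comparisons as planned.
- For the rate-dependent intervals (ST/QT and PQ), add an analysis conditional on RR. Either fit a regression on RR in the healthy group and express each CHD fetus as a deviation from it, or include RR as a covariate in the group comparison.
- Do not restrict the analysis to sinus beats.

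The signals are stored (sections 3, 5.1 and 10.1), so no extra visit or recording is needed. The cost is a little more extraction work, including a rhythm reading that section 6.3 does not now ask for, some further analysis, and two versions of some interval results to report.

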**Intervention**: The fECG is a non-invasive, transabdominal approach with self-adhesive electrodes. The recordings are performed between 08.00 h and 16.00 h during appointments at the outpatient clinic and will take no longer than 45 minutes. The patient will be lying on a comfortable bed in a semi-recumbent position.

**Main study parameters/endpoints:** to determine the normal values and ranges of amplitudes, segment intervals and heart axis of healthy fetuses with a gestational age of 18 to 24 weeks. To establish the differences in fECG between healthy fetuses and fetuses diagnosed with severe CHD.

**Nature and extent of the burden and risks associated with participation, benefit and group relatedness:** There is no risk associated with the recordings of the fECG. There might be some minor skin irritation caused by the self-adhesive electrodes. Measurements are combined with regular hospital visits.

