# 3. STUDY DESIGN

Both the cross-sectional and case-cohort study are prospective in nature. In the future, a longitudinal cross-sectional study can be performed based upon this study.

The cross-sectional study will take place in the MMC, Veldhoven, the Netherlands and Diagnostic center Eindhoven, the Netherlands. All the patients who visit the outpatient clinic for the first time will receive information about the research. Patients who visit the Diagnostic center Eindhoven will receive information about the research via their appointment confirmation e-mail. Measurements will be performed before or after the SEO or GUO-1 after written informed consent; patients do not have to come to the hospital or the diagnostic center for an extra visit.

The case-cohort study will take place in the MMC Veldhoven, and the medical centers Radboud MC Nijmegen, Academic Medical Center Amsterdam, and Maastricht UMC the Netherlands. Whenever a patient is diagnosed with a fetal severe CHD in any of these centers by using the SEO and the GUO, they will inform the patient about our research and contact us after informed consent. We will perform a fECG during routine follow up visits in those centers. For more information on recruiting the patients, see chapter 9, paragraph 9.2 “Recruitment and consent”.

In the cross-sectional study, 200 pregnant women will be included. With this amount of patients, we can determine with the wanted accuracy what the normal values and 95% CI of a healthy fetus are^9, 10^. If any of these fetuses is diagnosed with a CHD, they will automatically be evaluated in the case-cohort study.

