## 9.2 Recruitment and consent

The patients of the cross-sectional study will be recruited through the gynecology outpatient clinic and through the Diagnostic center Eindhoven. The patients will receive information about the research during the appointment at the outpatient clinic, when the SEO or GUO-1 will be planned or via e-mail with the confirmation of their appointment for a SEO at the Diagnostic center Eindhoven. This information contains all the aspects and details of the research. Attached to the patient information letter, the patients will find an informed consent form. If patients have any questions, one of the researchers will answer these questions. Before the fECG will be conducted, the researcher will explain the meaning of the research again. The time of consideration will vary between different patients.

The patients of the case-cohort study will be recruited after the SEO and they will have recently discovered that their baby has a form of severe CHD. The follow up will be provided by a gynecologist at MMC Veldhoven, Radboud MC Nijmegen, AMC Amsterdam or Maastricht UMC. These specialists will ask the patients if they want to join the research. They will receive the information letter. Attached to the patient information letter, the patients will find an informed consent form. If wanted, the researcher can provide some extra information before conducting the fECG. It is important to conduct the fECG before week 24. The time of consideration will vary between different patients.

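### Section 8 ignores gestational age although most CHD fetuses are recorded later than healthy ones; if fECG values change with age, the CHD comparison is confounded and the single normal range is poorly supported at the edges of 18 to 24 weeks

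*Protocol*

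**What the plan says.** **Analysis.** Protocol section 8 forms one group per CHD type and puts "all the healthy fetuses in one group". The intervals of the two studies "will be compared with one another through a t-test or a Mann-Whitney-Wilcoxon-test". Under its primary-parameter heading, section 8 defines the result as "The mean and standard deviation of the segment intervals and the amplitudes (with 95% confidence intervals) and the heart axis of healthy fetuses". The Summary states that these normal values are for "healthy fetuses with a gestational age of 18 to 24 weeks". Gestational age appears as an eligibility window (sections 4.1 and 4.2) but nowhere in the analysis: there is no covariate, stratum, matching or age-specific limit.

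**Timing, healthy fetuses.** Section 3: "Measurements will be performed before or after the SEO or GUO-1 after written informed consent". Section 1 places the SEO at about week 20. The protocol does not say when GUO-1 takes place.

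**Timing, CHD fetuses.** Section 9.2: "The patients of the case-cohort study will be recruited after the SEO". Section 3 requires diagnosis by SEO and GUO, and then: "We will perform a fECG during routine follow up visits in those centers". Section 9.2 adds an upper limit: "It is important to conduct the fECG before week 24".

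**Exception.** Under sections 3 and 6.3, a CHD found in the cross-sectional cohort, including one missed at the SEO, moves to the case-cohort study. Section 4.1 says such data are either excluded or analysed there. These fetuses were recorded at the same visit as the healthy ones.

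**The concern.** A two-sample test attributes any systematic difference between the groups to CHD. Here the groups also tend to differ in age at recording, because one is measured at the screening visit and the other, for the most part, after the diagnosis made from it. If an interval or amplitude changes between 18 and 24 weeks, part of the observed difference is maturation. It can imitate a CHD pattern or mask one, and recruiting more fetuses does not remove it.

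The primary objective is affected too. A single mean and SD is presented as valid for a six-week window, while recruitment concentrates the recordings around the SEO. Values near 18 and near 24 weeks would be judged against limits derived mainly from fetuses of another age. The secondary objective of diagnostic value (section 2) depends on the same limits.

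**Working it through.** **What can be reproduced.** The protocol gives no figure for this comparison: section 4.4 states that no sample size calculation was made for the case-cohort study. The healthy sample of 200 rests on a textbook reference without inputs and cannot be re-derived. The calculation below is therefore an illustration, not a check of a stated number.

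**Inputs from the protocol.** 200 healthy fetuses; 10 per CHD type (sections 4.1 and 4.4); window 18 to 24 weeks, so 6 weeks; SEO around week 20.

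**Assumptions not in the protocol.** Two-sided alpha 5%; no true CHD effect; linear drift D of 0 to 1.5 SD over 6 weeks, where SD is the spread at a fixed age; CHD recordings 1 to 2 weeks later on average; age at recording centred on week 20 with SD 0.8 weeks in the healthy group.

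**1. Bias of the crude comparison.** Bias = (D/6) × gap.
- D = 0: bias 0 for any gap.
- D = 0.5, gap 1: 0.5/6 × 1 = 0.08 SD.
- D = 1.0, gap 2: 1.0/6 × 2 = 0.33 SD.
- D = 1.5, gap 2: 1.5/6 × 2 = 0.50 SD.

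**2. Type I error, 10 against 200.** SE = √(1/10 + 1/200) = 0.324 SD. Age spread inflates it by √(1 + (D/6)² × 0.8²), which is at most 1.02. With λ = bias/SE, type I error = 1 − Φ(1.96 − λ) + Φ(−1.96 − λ).

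| D (SD over 6 weeks) | Gap (weeks) | Bias (SD) | λ | Type I error |
|---|---|---|---|---|
| 0 | 1 or 2 | 0 | 0 | 5% |
| 0.5 | 1 | 0.08 | 0.26 | 6% |
| 1.0 | 2 | 0.33 | 1.02 | 17.5% |
| 1.5 | 2 | 0.50 | 1.51 | 33% |

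**3. Simulation with the same age distribution.** 200 against 10, no true effect, 3000 runs (1500 for Mann-Whitney), gap 2 weeks:

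| Slope (SD per week) | t-test | Mann-Whitney | Regression with gestational age |
|---|---|---|---|
| 0 | 5.6% | 6.1% | 4.9% |
| 0.1 | 8.9% | 8.2% | 4.8% |
| 0.2 | 22.8% | 20.1% | 5.7% |
| 0.3 | 41.7% | 38.3% | 5.3% |

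The slope of 0.3 (1.8 SD over 6 weeks) lies beyond the range in step 2. Choosing the rank test does not help. Over all scenarios run (gap 0 to 3 weeks), the age-adjusted test stayed between 4.5% and 5.7%. With no gap, the crude t-test stayed near 5% at every slope.

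**4. Pooled range at the edges.** With ages centred on week 20, pooled SD = s = √(1 + (D/6)² × 0.8²). The share of healthy fetuses above the upper limit at 24 weeks is 1 − Φ(1.96s − 4D/6). The share below the lower limit at 18 weeks is Φ(−1.96s + 2D/6). For an upward drift, against a nominal 2.5%:

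| D | Above upper limit at 24 weeks | Below lower limit at 18 weeks |
|---|---|---|
| 0 | 2.5% | 2.5% |
| 0.5 | 5.1% | 3.6% |
| 1.0 | 9.5% | 5.0% |
| 1.5 | 15.9% | 6.7% |

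**5. How much the exception dilutes this.** At the protocol's 4 to 9 per 1000, 200 women yield 200 × 0.004 = 0.8 to 200 × 0.009 = 1.8 fetuses with any CHD, against 60 planned cases. Referral to GUO-1 could raise that number.

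**The case against.** The strongest objection is that the protocol contains no evidence of a trend. It gives no change in intervals, amplitudes or axis between 18 and 24 weeks, and no actual ages at recording. With no drift or no gap there is no error. This stands, and it makes the point conditional. A reader might infer that the single range is simply wrong at 18 and 24 weeks; the protocol does not support that.

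A reader might also infer that every CHD fetus is recorded later. The exception for the cross-sectional cohort contradicts this, and GUO-1 recordings of healthy fetuses may narrow the gap. What stands is a tendency built into recruitment, not a rule.

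Both groups share the same window, which caps the gap. The comparison is secondary, in a self-described pilot that aims only at large differences (section 4.1) and has no effect on care. Ten against 200 has 80% power only for about 0.91 SD, beside which a bias of 0.08 SD is negligible; 0.50 SD is not. It is tempting to quote far larger error rates for all 60 cases against 200, but section 8 compares by CHD type, so that test is not planned.

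Finally, covariate detail is often left to an SAP, which may exist. Here, however, section 8 names the pooled group and the crude tests, so a later SAP would have to depart from the protocol to adjust for age.

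**Conclusion.** The point holds in conditional form. Section 8 fixes an unadjusted comparison and one pooled healthy range, while sections 3 and 9.2 make most CHD recordings later than the healthy ones. To the extent that fECG parameters change with gestational age, the CHD comparison is confounded by age and the single range is inaccurate towards 18 and 24 weeks. Whatever the trend, the range is thinly supported there if recordings cluster around the SEO. Under the stated assumptions the bias runs from 0 to 0.50 SD and the type I error from about 5% to 33% for 10 against 200. These figures rest on an assumed drift and gap, and their lower end is no problem at all. No sample size in the protocol is shown to be wrong by this. The case for changing section 8 is that the plan gives no ground for assuming a flat trend and the protection is nearly free.

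**What to change.** Amend section 8 before analysis:

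1. Record exact gestational age (weeks and days) at each fECG.
2. In the healthy fetuses, model the mean of each parameter, and the SD if needed, as a simple function of gestational age. Report age-specific limits only over ages where the data support them. If recordings cluster near the SEO, either state a narrower range of validity or spread recruitment over the window; modelling alone cannot supply limits at ages with few recordings.
3. Make the main comparison of each CHD group with the healthy group a regression with gestational age as covariate, or a comparison of gestational-age z-scores from the healthy model. Keep the crude t-test or Mann-Whitney test as a secondary analysis.
4. Tabulate age at recording by group, so that the actual gap is visible.

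Cost: a protocol amendment, a little more analysis work, and one or a few degrees of freedom per parameter. Gestational age must already be known for every woman to establish eligibility, so items 1, 3 and 4 need no extra patients or visits. Only a decision to spread recruitment over the window would affect the conduct of the study.
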